### Concealment mechanism

This is an open study. Patients, physicians, and other care-givers are notified of the randomization group to which the patient is allocated.

### Implementation

The principal investigator of each establishment concerned promises to conduct the clinical trial in conformity with the protocol which has been approved by the Ethic Committee and the competent authority.

The principal investigator should not modify any aspect of the protocol without prior written permission from the Sponsor nor without the approval of the proposed modifications by the Ethic Committee and the competent authority.

The Principal Investigator is responsible for:Providing the Sponsor with his/her CV as well as that of co-investigators,Ensuring co-investigators and other healthcare professionals should be sufficiently qualified by education, training, and experience to perform their tasks,Identifying members of his/her team participating in the trial and defining their responsibilities,Recruiting patients after receiving the Sponsor’s approval.

Each investigator is responsible for:Personally obtaining the informed consent form which has been dated and signed by the participant in the research prior to any specific trial selection procedure,Regularly completing the case report form (CRF) for each patient included in the trial and ensuring that the Clinical Research Assistant (CRA) mandated by the Sponsor has direct access to source documents in order to validate information on the CRF,Dating, correcting, and signing the corrections on the CRF for each patient included in the trial,Accepting regular visits from a CRA and possibly visits from auditors mandated by the Sponsor or inspectors from the regulatory authorities.

All documentation concerning the trial (protocol, consent form, case report form, investigator file, etc.), as well as the original documents (laboratory results, imaging studies, medical consultation reports, clinical examination reports, etc.), is considered confidential and will be kept in a safe place. The Principal Investigator will keep data as well as a list of patient-identifying data for at least 15 years after the end of the study, or more if specified by the local regulation.

## Assignment of interventions: blinding

This is an open trial, due to the surgical nature of the interventional groups. No blinding will be performed. The data will be anonymized so that the data analyst will be blinded as to group allocation.

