#### Secondary objectives

To compare total thyroidectomy and radioactive iodine (^131^I) to total thyroidectomy with bilateral prophylactic central compartment neck dissection and 131I in terms of:Thyroglobulin levels after surgery alone (usTg/T4) measured while on T4 treatment, 8+/−2 weeks postoperatively, before stimulation and administration of radioactive iodinePercent of patients in complete remission (excellent response) at 3 and 5 years after randomization, as defined by a normal neck ultrasound and usTg/LT4 ≤ 0.2 ng/m. The endpoint of 5 years reflects the data from a prospective multicenter study of 715 patients reporting that 81% of recurrences occurred within 5 years,[43] and from a retrospective study of 1020 patients followed for 10 years reporting that all structural recurrences occurred within 8 years, with 77% occurring within 5 years [44].Percent of patients at 1, 3, and 5 years after randomization with structural incomplete response in the neck defined by a malignant lesion in the neck detected by ultrasound and confirmed by cytology (and/or Tg in the needle washout fluid >10ng/ml). Cytology will be mandatory for suspicious lesions measuring 8mm or more in the smallest diameter; lesions with suspicious features on ultrasound but measuring <8 mm may undergo cytology at the discretion of the center’s principal investigators.Percent of patients at 1, 3, and 5 years after randomization with biological incomplete response defined by a normal neck ultrasound and absence of disease detected on other conventional or metabolic imaging (^131^I, ^18^FDG-TEP), if performed, associated with a serum Tg/LT4>0.2 ng/mlPercent of patients at 1, 3, and 5 years after randomization with an indeterminate response defined by a suspicious lesion on neck ultrasound without cytological proof of disease and/or detection of TgAbPercent of patients at 1, 3, and 5 years after randomization with diagnosis of distant metastases on metabolic imaging (^131^I, ^18^FDG-TEP) or cross-sectional imaging, and confirmed cytologically (except for metastases with ^131^I uptake) or with repeat imaging at 6 months (if cytology not possible)Percent of patients at 1, 3, and 5 years after randomization having undergone further treatment (surgery or 2nd therapeutic administration of ^131^I, number of retreatments per patient and indication for each retreatment)At 1 year: percent of patients with persistent hypoparathyroidism with supplementation and/or persistent vocal fold paralysis; subjective dysphonia (Voice Handicap Index)[45] and dysphagia (SWAL-QOL)[46] (questionnaires in their validated French versions) compared between groups after randomization: Quality of life SF36[47], EuroQol EQ-5D,[48] Anxiety (State-Trait Anxiety Inventory-STAI)[49]Cost-utility analysis.

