## Interventions

### Explanation for the choice of comparators

The primary objective of this study is to assess the non-inferiority of total thyroidectomy alone as compared to total thyroidectomy with bilateral prophylactic central compartment neck dissection in terms of the rate of complete remission (excellent response) at 1 year after randomization, for differentiated thyroid cancer cT1bT2N0.

Group 1 (reference group): total thyroidectomy with bilateral prophylactic central compartment (level VI) neck dissection as defined by the American Thyroid Association [38]. This is a standard treatment recognized by the French Society of Otolaryngology Head and Neck Surgery [15]. The number of lymph nodes resected, the number of metastatic nodes, their size, and the presence or absence of extranodal spread will be recorded. Due to the large natural variability of the number of lymph nodes retrieved in a PND, [53] no patient will be excluded on the basis of number of lymph nodes.

Group 2 (“experimental” group): total thyroidectomy alone without neck dissection. This is recognized as a standard treatment by the Francophone Association of Endocrine Surgery [19].

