### Outcomes: Primary criterion

The primary criterion is the rate of patients *in complete remission (excellent response) at 1 year after radomization* as defined by the presence of the 3 criteria:Normal whole body scan (SPECT-CT) at the time of administration of ^131^I [SPECT-CT will be performed 2–5 days after the administration of 30 mCi (1.1 GBq) of ^131^I after stimulation using injected recombinant human TSH (rhTSH)],Normal neck ultrasound at 8+/−2 months after ^131^I administrationUnstimultaed ultrasensitive thyroglobuline while on L-thyroxine treatment (usTg/LT4) ≤ 0.2 ng/mL without anti-Tg antibodies (TgAb) at 8+/−2 months after ^131^I administration

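### The reason given for an unblinded trial does not cover the readers of the SPECT-CT and 1-year ultrasound, each of whom can decide the primary endpoint

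*Protocol article*

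**What the plan says.** Under Assignment of interventions: blinding, the trial is declared open because the groups differ by surgery, and the rule is stated without exception for outcome readers: "No blinding will be performed. The data will be anonymized so that the data analyst will be blinded as to group allocation". The one exception, in the second sentence of that quote, concerns the analysis stage. Concealment mechanism adds: "Patients, physicians, and other care-givers are notified of the randomization group to which the patient is allocated". Image readers are not named there. However, Criteria for eligibility of participating centers lists radiologists and nuclear medicine physicians among the participating practitioners, so on a plain reading they are included.

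The primary criterion needs three things together. Two are readings made by a person: "Normal whole body scan (SPECT-CT) at the time of administration of" radioiodine, and "Normal neck ultrasound at 8+/−2 months after" it. The third is a laboratory result: unstimulated thyroglobulin at or below 0.2 ng/mL without anti-thyroglobulin antibodies. The article describes no masked, independent or central reading of either image. The Follow-up section does tie suspicious ultrasound lesions to published standardised criteria.

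**The concern.** A surgeon cannot be masked to the operation, and a patient perhaps cannot be. The reader of a scan taken 2 to 4 months after surgery, or of an ultrasound at about 1 year, is in a different position: the reading can be recorded before the reader is told which operation was done. The stated reason therefore supports open surgery but not open outcome reading.

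All three criteria must be met, so a single abnormal call on either image is enough to fail the patient. Some of these calls are not clear-cut. The article's own definition of indeterminate response (Oncologic secondary criteria) allows for non-specific imaging findings and faint uptake in the thyroid bed. Knowing whether the central compartment was dissected could plausibly tilt such a call. With few failures expected and a 5-point margin, a small difference between arms in how borderline images are called could help thyroidectomy alone pass or make it fail.

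**Working it through.** **Inputs from the protocol article** (Determination of sample size): margin 5 points, one-sided 0.025, power 80%, 299 per group. Cited remission rates are 94% and 90.2%. The rate used for planning is not stated.

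**Reproducing 299.** n = (1.960 + 0.842)² × 2p(1 − p) / 0.05². With p = 0.95 in both arms this is 298.3, rounded up to 299 per arm and 598 in total. It matches exactly, so 95% is the inferred planning rate. The cited rates would give 355 (94%) and 556 (90.2%) per arm.

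**How few patients matter.** Five points is 0.05 × 299 ≈ 15 patients. Suppose 284 of 299 are in remission in the dissection arm. Use the Wald lower limit at the one-sided 0.025 level:
- 3 fewer remissions with thyroidectomy alone: −0.0100 − 1.960 × 0.01867 = −0.0466, a pass.
- 4 fewer: −0.0134 − 1.960 × 0.01893 = −0.0505, a fail.

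With the one-sided 95% interval named in the Statistical methods section, up to 5 fewer would pass.

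**Effect of a differential reading shift.** Let s be the net shift in the composite remission rate of the thyroidectomy-alone arm. The values of s are assumptions; the documents give no reading-error rate. SE = √[(p₁(1 − p₁) + p₂(1 − p₂)) / 299].

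*Arms truly equal at 95%, shift against thyroidectomy alone:* power = Φ((0.05 − s)/SE − 1.960).
- s = 0: SE 0.01782, power 80.1%
- s = 1 point: SE 0.01864, power 57.4%
- s = 2 points: SE 0.01941, power 33.9%

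*True rates 95% and 90%, shift in favour of thyroidectomy alone:* false non-inferiority = Φ(s/SE − 1.960).
- s = 0: 2.5%
- s = 1 point: SE 0.02080, 7.0%
- s = 2 points: SE 0.02013, 16.7%

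Exact binomial enumeration of the same rule agrees closely: 80.5%, 58.3% and 35.2% for power; 2.8%, 7.7% and 17.8% for false non-inferiority.

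**Range over the reference rate** (same formulas, s = 0, 1 and 2 points; for false non-inferiority the true rate with thyroidectomy alone is 5 points lower):

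| Reference rate | Power | False non-inferiority |
|---|---|---|
| 95% | 80%, 57%, 34% | 2.5%, 7.0%, 16.7% |
| 94% | 73%, 51%, 30% | 2.5%, 6.6%, 15.2% |
| 90.2% | 54%, 36%, 22% | 2.5%, 5.7%, 11.8% |

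**What a shift of that size requires.** A favourable miscall rescues only a patient who fails on that image alone. At 90% remission the failures are 10% of the arm, so a 2-point shift needs 2/10 = 20% of all failures to be image-only failures called normal, net of opposite errors. A 1-point shift needs 10%. In the other direction less is needed: at 95% remission, a 1-point shift means about 1/95 = 1.1% of patients in remission being called abnormal.

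**The case against.** Several counter-arguments have force.

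- **The shifts are assumed.** No document gives a reading-error rate, and the 95% rate is inferred. The calculation shows how sensitive the conclusion is, not how large the bias will be. If most failures come from thyroglobulin or its antibodies, the images have less room to matter. This stands.
- **Discretion is already limited.** The standardised ultrasound criteria leave less to the reader. This stands as mitigation, but criteria do not hide the arm.
- **Masking is hard here.** Patients know their arm and are present at the ultrasound, and nuclear medicine physicians also give the radioiodine and may take consent. Accrual began in August 2018, so some images have already been read openly. This limits what the change can achieve, but does not make the stated reason fit the readers.

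A reader might also infer three stronger points, which the documents do not support.

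- **That biopsy discretion threatens the margin.** For small lesions the article says "lesions with suspicious features on ultrasound but measuring <8 mm may undergo cytology at the discretion of the center’s principal investigators". Under Secondary objectives, cytology separates indeterminate from structural incomplete response, and neither counts as excellent response. Cytology is not in the primary criterion. Who decides on biopsy is also a clinical matter.
- **That the image readers have a stake in the answer.** The opposed French recommendations in the Introduction come from two surgical societies. Nothing reports a position held by radiologists or nuclear medicine physicians.
- **That the analyst's masking is shown to fail.** The article records "The number of lymph nodes resected, the number of metastatic nodes, their size" in the dissection group, which could reveal the arm. However, it does not say that these fields enter the primary analysis file, and such detail commonly sits in a plan not shown here.

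**Conclusion.** The point holds in a limited form. The protocol rules out blinding for a reason that applies to the operation, and thereby leaves two reader-dependent components of the primary endpoint open to knowledge of the arm. At the planned size, with 284 of 299 remissions in the dissection arm, a fourth lost remission with thyroidectomy alone reverses the conclusion. A net differential shift of 1 or 2 points would cut power from 80% to about 57% or 34% if the arms are equal, or raise false non-inferiority from 2.5% to about 7% or 17% if thyroidectomy alone is 5 points worse.

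These figures rest on 95% remission in the dissection arm, 299 evaluable patients per arm, the one-sided 0.025 level and assumed shift sizes. They do not show that bias will occur or which arm it would favour. The case for change is that a partial safeguard is cheap.

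**What to change.** Amend Concealment mechanism and Assignment of interventions: blinding so that they separate open treatment from outcome reading. Where feasible, the centre's existing SPECT-CT and 1-year ultrasound readers should not be given the arm, operative report or nodal pathology until they have recorded normal or abnormal for the primary endpoint. After that, full information is available for care. Record for each image whether the reading was masked, and report this, since images already read will remain open.

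For the per-protocol population, decide evaluability as to follow-up tests and anti-thyroglobulin antibodies from a listing that shows neither arm nor node counts.

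The cost is an amendment, a change to request and report forms, and some local organisation where the reader also treats the patient. No extra readers or examinations are needed, and the sample size stays at 598. Masking will be incomplete, because the patient knows the arm and some readers will infer it.

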### Data collection and management

#### Plans for assessment and collection of outcomes

The Biostatistics and Epidemiology unit at Gustave Roussy will implement electronic CRF (eCRF) using adequate software, thus allowing safe online direct data collection. Quality of life questionnaire will be completed using paper questionnaire.

Each user will have personal identifiers (user ID / password), and data access will be strictly limited according to profiles.

For each patient included in the trial, the eCRF will have to be completed by the hospital CRA and signed by the investigator or the person designated by the investigator.

The study can be interrupted or terminated by the sponsor at any time in agreement with the coordinating investigator. Reasons may include, but are not limited to, the following:Frequency and/or unexpected severity of the toxicity,If any information leads to doubt as to the benefit/risk ratio of the clinical trialRecruitment of patients too low,Poor quality of the data collected

The Sponsor has the possibility to replace a site at any time. Reasons for replacing a site may include, but are not limited to, the following:Slow recruitmentPoor protocol adherence / serious breach to the protocolInaccurate or incomplete data recordingNon-compliance with the International Conference on Harmonisation (ICH) guideline for Good Clinical Practice.

The Sponsor can temporarily or permanently discontinue an investigator for participation in the clinical trial at any time. Reasons may include, but are not limited to, the following:Poor protocol adherence / serious breach to the protocolMajor deviation from the protocolNon-compliance with the International Conference on Harmonisation (ICH) guideline for Good Clinical Practice.

Serious breach is defined as any conditions, practices, or processes that adversely affect the rights, safety, or well-being of the subjects and/or the quality and integrity of data.

Major deviation is defined as any conditions, practices, or processes that might adversely affect the rights, safety, or well-being of the subjects and/or the quality and integrity of data.

Minor deviation is defined as any conditions, practices, or processes that would not be expected to adversely affect the rights, safety, or well-being of the subjects and/or the quality and integrity of data.

#### Plans to promote participant retention and complete follow-up

The investigator is responsible for the appropriate medical follow-up of patients until resolution or stabilization of the adverse event or until the patient’s death. This may mean that follow-up should continue once the patient has left the trial.

Follow-up information about a previously reported serious adverse event must be reported by the investigator to the Pharmacovigilance Unit within 24 h of receiving it (on the serious adverse event report form, by ticking the box marked Follow-up N°…). The investigator also transmits the final report at the time of resolution or stabilization of the SAE.

The investigator retains the documents concerning the supposed adverse event so that previously transmitted information can be completed if necessary.

#### Data management

The eCRF will gather both clinical data and quality of life questionnaire (EQ-5D, Voice Handicap Index, SWAL-QOL, SF 36, and STAI) data.

Data collected will be managed in the Biostatistics and Epidemiology unit at Gustave Roussy.

The data collected through the eCRF will be the source data for the analysis. All the statistical analyses will be performed at the Biostatistics and Epidemiology Unit of Gustave Roussy. Therefore, no data transfer will be needed.

In order to guarantee the authenticity and the credibility of the data in conformity with good clinical practices, the Sponsor has installed a quality assurance system which includes:Trial management in accordance with the procedures at Gustave Roussy,Quality control of data at the investigating site by the Clinical Research Assistant (CRA) in accordance with the monitoring plan,Possible auditing of investigating centres.

#### Confidentiality

The investigator promises, on his/her behalf as well as that of all the persons involved in the conduct of the trial, to guarantee the confidentiality of all the information provided by Gustave Roussy until the publication of the results of the trial.

All publications, abstracts, or presentations including the results of the trial require prior approval of the Sponsor (Gustave Roussy).

All oral presentations, manuscripts must include a rubric mentioning the Sponsor, the investigators / institutions that participated in the trial, the cooperative groups, learned societies which contributed to the conduct of the trial, and the bodies which funded the research.

The Study Investigator-Coordinator will write an article reporting on the results as soon as possible after the final analysis and will be the first author of the publication.

The principal investigator will specify the other authors (other investigators, statistician…) in conformity with “Uniform requirements for manuscripts submitted to biomedical journal” (http://www.icmje.org/).

#### Plans for collection, laboratory evaluation, and storage of biological specimens for genetic or molecular analysis in this trial/future use

Each participating center will retain pathology specimens as per French laws, health authorities’ biobanking decrees and routine standard of care, which may be accessed for future studies.

### Statistical methods

#### Statistical methods for primary and secondary outcomes

Descriptive summary statistics will be provided for continuous demographic, laboratory, and clinical variables. The descriptive summary statistics will include number of patients, means and standard deviations for quantitative variables, and percentages for qualitative data.

Subject demographic and baseline characteristics will be summarized by treatment group. The Student test will be used for the continuous variables (or non-parametric test if variables are not normally distributed), and the chi-square test will be used for the categorical variables.

Primary outcomes s1

The main endpoint will be analyzed 1 year after randomization of the last patient, once all the CRF will have been collected and the database has been cleaned. The analysis will be performed when all patients will have 1 year of follow-up, and no lost of follow-up will be tolerated.

A patient will be in remission if the requirements are met at 1 year following randomization. Conversely, a patient will be considered to not be in remission if the criteria are not met at 1 year following randomization. In the absence of censored data, the proportion of patients in complete remission will be calculated as a percentage.

Since the study is designed as a non-inferiority study, the primary analysis will be carried out by considering all evaluable patients (per-protocol population), as this is the most conservative approach in this context. Patient will be considered as evaluable if the treatment and the follow-up conform to the study protocol (diagnostic tests performed) and if the patient does not have detectable anti-Tg antibodies. A sensitivity analysis using the intent-to-treat (ITT) population, considering all patients in their initial group of randomization, will also be performed, to test the robustness of the results.

The observed difference in patients in complete remission (∆) and its 95% unilateral confidence interval will be calculated. If the unilateral confidence interval does not include the −5% clinically relevant difference (∆L), then the TT alone strategy will be considered as non-inferior to the TT + PCND strategy.

All statistical analyses will be performed using the SAS® software.

Secondary outcomes s1Unstimulated thyroglobulin levels between groups will be compared between groups using a chi-square test.The rate of patients in complete remission at 3 and 5 years will be compared between groups using a chi-square test.The rate of patients in with structural incomplete response, biological incomplete response, indeterminate response, distant metastases, or further treatments at 1, 3, and 5 years will be compared between the 2 groups using a chi-square test for each type of response.

For these secondary criteria we expect, based on retrospective series comparing the two surgical techniques (total thyroidectomy alone or total thyroidectomy + PND), rates of incomplete response or re-treatement in the range of the following:Difference in locoregional control = 6.9% at 10 years [1]Difference in rate of recurrence = 4.6% at 3 years [2]Difference in rate of retreatment = 8.2% at 5 years [3]Rate of structural recurrence = 1.4% at 8 years [44]The rate of patients at 1 year with persistent hypoparathyroidism requiring medication and/or with persistent vocal fold paralysis will be compared between groups using a chi-square test; subjective dysphonia (Voice Handicap Index) and subjective dysphagia (SWAL-QOL) toxicities will be compared using a Student test for each time of evaluation (or a Kruskall-Wallis non-parametric test if they are not normally distributed).Quality of life and anxiety: The investigator will inform the patient on the objective of QoL data collection. QoL data may be not exploitable in case of great number of missing questionnaires. Data will be analyzed according to the scoring manual of each questionnaire. A longitudinal analysis using a mixed model will be used to take into account of repeated QoL assessment and the initial value. If this analysis shows a significantly different effect between groups or an interaction between treatment and time, an analysis of the treatment effect on quality of life will be carried out at each time. Mean sub-scale scores will be compared using a Student test for each time of evaluation (or a Kruskall-Wallis non-parametric test if they are not normally distributed).

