**Trial design and methods:**

Prospective randomized open multicenter phase III trial including patients with 11–40-mm papillary thyroid carcinoma (Bethesda VI) or suspicious cytology (Bethesda V) confirmed malignant on intra-operative frozen section analysis, with no suspicious lymph nodes on a specialized preoperative ultrasound examination. Patients will be randomized 1:1 into two groups: the reference group total thyroidectomy with bilateral prophylactic central neck dissection, and the comparator group total thyroidectomy alone. All patients will receive an ablative dose of 30mCi of radioactive iodine (RAI) within 4 months of surgery. The primary outcome is to compare the rate of excellent response at 1 year after surgery between the groups, as defined by an unstimulated serum thyroglobulin (Tg) level ≤ 0.2 ng/mL with no anti-Tg antibodies, an normal neck ultrasound and no ectopic uptake on the post-RAI scintiscan. Non-inferiority will be demonstrated if the rate of patients with excellent response at 1 year after randomization does not differ by more than 5%. Setting the significance level at 0.025 (one-sided) and a power of 80% requires a sample size of 598 patients (299 per group). Secondary outcomes are to compare Tg levels at 8 +/− 2 postoperative weeks, before RAI ablation, the rate of excellent response at 3 and 5 years, the rate of other responses at 1, 3, and 5 years (biochemical incomplete, indeterminate, and structurally incomplete responses), complications, quality of life, and cost-utility.

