Our study differs from these published studies in the following ways:Our study includes only tumors ≥11 mm (microcarcinomas are not eligible), whereas all of the studies cited in Table 1, with the exception of the study by Sippel et al. [32], included a large proportion of microcarcinomas (in Ahn et al. [31] for example, 90% of the tumors were T1 with a mean tumor size of 1.1 +/− 0.6 cm);Thyroglobulin measurements will be evaluated before and after the administration of RAI to evaluate the effect of RAI ablation and eliminate this bias found in most of these studies in which outcomes were evaluated after RAI ablation in most or all patients;Finally, our study is designed with a non-inferiority margin of 5% and an alpha level set at 0.025, whereas the study by Viola et al. [34] is significant but with a non-inferiority margin of 15% and an alpha of 0.05.

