### Determination of sample size

Non-inferiority will be demonstrated if the rate of patients in complete remission at 1 year after randomization does not differ by more than ΔL=−5%. Setting the significance level at 0.025 (one-sided) and a power of 80% requires a sample size of 598 patients without Tg antibodies (299 per group) (Nquery software).

In this network’s previous study, 94% of the low-risk patients (including 12% T2N0) were in complete biological remission at 1 year after randomization [40]. In a similar prospective multicenter trial, 90.2% of the low-risk patients, including patients T1-T3 N0-N1 with or without central compartment neck dissection, were in complete biological remission at 1 year [42].

If 5% secondary exclusion (final histopathology not differentiated thyroid cancer): 628 patients are required for randomization.

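### The primary decision rule uses a one-sided 95% confidence interval (one-sided alpha 0.05), although the trial is declared and sized at one-sided alpha 0.025

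*Protocol article*

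**What the plan says.** Three places in the protocol article fix the error rate.

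- Abstract, Trial design and methods: "Setting the significance level at 0.025 (one-sided) and a power of 80% requires a sample size of 598 patients (299 per group").
- Determination of sample size: the same level, "Setting the significance level at 0.025 (one-sided) and a power of 80"%, with a margin of −5%.
- Background and rationale, in the comparison with published studies after Table 1: "our study is designed with a non-inferiority margin of 5% and an alpha level set at 0.025". This is set against an earlier single-centre randomised trial described as "with a non-inferiority margin of 15% and an alpha of 0.05".

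The interval-based decision rule appears in Statistical methods for primary and secondary outcomes. The remission difference is estimated and "its 95% unilateral confidence interval will be calculated". If that interval, again called unilateral, excludes −5%, "then the TT alone strategy will be considered as non-inferior to the TT + PCND strategy".

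**The concern.** A confidence limit and a one-sided test correspond exactly: a one-sided limit at level 1 − α gives a test at one-sided α. A one-sided 95% limit uses z = 1.645 and tests at 0.05. The limit that matches 0.025 is the one-sided 97.5% limit, with z = 1.96, which is also the lower end of the ordinary two-sided 95% interval. The analysis section therefore specifies a more lenient test than the one the design declares.

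This rule decides the trial's main conclusion. The section on the choice of comparators says that confirmed non-inferiority could lead to prophylactic neck dissection being abandoned in these patients. A result that passed at 0.05 but not at 0.025 would satisfy the written rule and fail the declared standard. If the conflict is still open when the data are seen, either choice of limit can be criticised as made after the fact.

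**Working it through.** **Inputs from the article.** One-sided significance level 0.025, power 80%, margin 5 points, 299 per arm (abstract; Determination of sample size); decision interval 95% one-sided (Statistical methods); cited remission rates 94% and 90.2% (Determination of sample size).

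**Assumptions.** The article does not state the planning remission rate, so 95% is assumed below and the two cited rates are shown beside it. The method for the interval is not named, so an unpooled (Wald) limit is used.

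**Step 1: the stated sample size.** With equal true rates p, n per arm = (z₁₋α + z₀.₈₀)² × 2p(1 − p) / 0.05².

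- α = 0.025, p = 0.95: (1.96 + 0.8416)² × 2 × 0.95 × 0.05 / 0.0025 = 298.3, rounded up to 299. This matches the stated figure.
- α = 0.05, p = 0.95: (1.645 + 0.8416)² × 0.095 / 0.0025 = 234.9, rounded up to 235.
- At the cited 94%: 355 (α = 0.025) or 279 (α = 0.05). At 90.2%: 556 or 438.

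The figure of 299 is thus consistent with 0.025 at 95%. It would also arise at α = 0.05 with p of about 93.5%, so this step alone does not identify alpha.

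**Step 2: probability of a false claim at the margin.** Full enumeration of two binomials, 299 per arm, true rate in the thyroidectomy-alone arm exactly 5 points below the reference. Non-inferiority is claimed if the difference − z × SE exceeds −0.05.

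| Reference rate | Written rule (z = 1.645) | Declared level (z = 1.96) |
|---|---|---|
| 95% (assumed) | 5.57% | 2.84% |
| 94% (cited) | 5.46% | 2.75% |
| 90.2% (cited) | 5.22% | 2.62% |

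The ratios are 1.96, 1.99 and 1.99. The small excess over the nominal 5% and 2.5% comes from the Wald approximation.

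**Step 3: how far the bar moves.** At 95% in both arms, SE = √(2 × 0.95 × 0.05 / 299) = 1.78 points. The half-widths are 1.645 × SE = 2.93 and 1.96 × SE = 3.49 points. The largest observed deficit that still passes is therefore about 5 − 2.93 = 2.07 points under the written rule and 5 − 3.49 = 1.51 points at the declared level.

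**Step 4: a data set on which the two rules disagree.** Thyroidectomy alone 279/299 = 93.31%; with dissection 284/299 = 94.98%; difference −1.67 points. SE = √(0.9331 × 0.0669/299 + 0.9498 × 0.0502/299) = 1.92 points.

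- Written rule: −1.67 − 1.645 × 1.92 gives −4.83% (unrounded SE), above −5%, so non-inferior.
- Declared level: −1.67 − 1.96 × 1.92 gives −5.43%, below −5%, so non-inferiority not shown.

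**Step 5: power with 299 per arm, equal true rates (normal approximation).** At 95%: 80.1% with z = 1.96 and 87.7% with z = 1.645. At 94%: 73.1% and 82.4%. At 90.2%: 53.8% and 66.0%.

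**The case against.** The strongest reply is that the phrase is a slip for the lower limit of the usual two-sided 95% interval. The article states 0.025 three times and presents it as a strength, so that reading is plausible. But the text calls the interval unilateral in both sentences of the rule and nowhere mentions a two-sided interval, so a statistician following it would use 1.645. The reply explains how the conflict may have arisen; it does not remove it. It does mean that the doubling of the error rate is conditional on the rule being applied as written.

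Three narrower objections stand. First, the planning rate is not stated, so the 299 back-calculation does not prove which alpha was used; the evidence for 0.025 is its express statement. Second, the article does not say whether the earlier trial's 0.05 was one- or two-sided, so it cannot be said that this trial would run at the same level as that one. Third, no statistical analysis plan is shown, and it may already have the right limit. None of these reconciles the passages. Nor does condensation into an article account for the conflict, since both levels are stated outright.

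**Conclusion.** The concern holds. The decision rule in the Statistical methods section contradicts the significance level in the abstract, the background and the sample size section. If it is applied as written, the nominal one-sided error is 0.05 instead of 0.025. The enumerated false-claim rate is about doubled at every reference rate tried (5.2% to 5.6% against 2.6% to 2.8%), so the conclusion does not depend on the unstated planning rate. It does rest on 299 evaluable patients per arm and a Wald limit. Observed deficits between about 1.5 and 2.1 points (at an assumed 95%) would pass one rule and fail the other. The point must be fixed before the primary analysis because it governs the main conclusion.

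**What to change.** In Statistical methods for primary and secondary outcomes, replace the one-sided 95% interval with wording such as: the two-sided 95% confidence interval of the difference (thyroidectomy alone minus thyroidectomy with dissection) will be calculated, and non-inferiority will be concluded if its lower limit, equivalently the one-sided 97.5% lower limit, lies above −5%. Check that any statistical analysis plan uses the same limit, and date the correction before outcome data by arm are examined.

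The cost is one sentence. The stated 598 patients need not change, because that number is already declared to be at one-sided 0.025; conduct and data collection are unaffected. The power under the corrected rule still depends on the unstated planning rate (80.1% at 95%, 73.1% at 94%). That is a separate matter and no reason to keep the more lenient limit.
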